## Abstract

**Introduction::**

Although balance problems in older populations are directly correlated with hip fractures, the overall physical gain afforded by balance rehabilitation itself has not yet been fully investigated. Here we describe a protocol for an open-label clinical trial to evaluate the effectiveness of computer-based balance-specific exercise (BSE) on the performance and balance of elderly women who underwent hip fracture surgery (HFS).

**Methods and analysis::**

Elderly female patients (≥65 years old) who underwent surgery for femoral neck, intertrochanteric, or subtrochanteric fracture regardless of surgery type will be included. The BSE will be conducted using a computed posturographic system for a 2-week intervention period following HFS. The primary outcome of this study is Berg balance scale score. All functional outcomes will be measured at 1 and 3 weeks and at 3 and 6 months after the surgical intervention. The data will be analyzed using the intention-to-treat principle.

## Introduction

1

### Background

1.1

A balance problem is both the cause and the result of hip fracture. In particular, elderly people who have undergone hip fracture surgery (HFS) suffer from balance problems. Radosavljevic et al^[1]^ reported a significant correlation between patient age and Berg balance scale (BBS) score at 3 months after HFS. Also, elderly individuals are afraid of falling after HFS and thus lack both balance confidence and functional balance.^[2]^ Portegijs et al^[3]^ suggested that balance confidence was independently correlated with mobility in patients with fall-related hip fractures. One study also suggested that balance confidence was highly correlated with activities of daily living (ADLs).^[4]^ Therefore, balance impairment may be a long-term issue among older adults after HFS and may limit mobility and daily activities and increase the risk of subsequent falls.^[5]^ Thus, balance impairment should be evaluated as a major fall risk and balance rehabilitation is essential to the prevention of additional falls in elderly individuals after HFS. The American College of Sports Medicine and the American Heart Association have also suggested that community-dwelling older adults at substantial risk of falls should perform exercises that maintain or improve balance to reduce the risk of injury.^[6]^

Most rehabilitation programs after HFS mainly focus on postoperative range of motion exercises, standing, gait training with progressive weight bearing, and strengthening exercises of the hip extensor and abductor muscles. These postoperative programs have been shown to improve the independence of ADLs and gait function after hip fracture.^[7]^ However, in long-term follow-up studies > 1 year, conventional rehabilitation programs had no significant effect on re-fracture and fall rates.^[8]^

Therefore, recent clinical trials about comprehensive rehabilitation after HFS included balance training to strengthen physical functioning and performance with the intention of improving gait and balance.^[9,10]^ One clinical trial also showed that the fall rate was reduced when individualized fall prevention programs were administered to elderly patients who were transferred to the rehabilitation department after HFS.^[11]^ However, those studies were limited to home-based exercises or outpatient rehabilitation programs after general rehabilitation of hip fracture and not about intensive balance training in the early postoperative stage. The overall physical gain by balance rehabilitation itself has not yet been fully investigated. Furthermore, balance training immediately after HFS is fundamentally limited for patients whose balance confidence is low and who still suffer from severe surgical-site pain. Therefore, clinical studies should be conducted to evaluate the effectiveness of systematic and safe balance rehabilitation in patients after hip fracture.

### Objectives

1.2

We aim to evaluate the effectiveness of a computer-based balance specific exercise (BSE) on the performance and balance ability of the elderly women who underwent HFS. We will also investigate whether the intervention could reduce their fear of falling and improve their coping abilities.

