### Trial design

2.1

This prospective and open-label clinical trial will be performed in a tertiary hospital setting. During the 2-week postoperative intervention period, patients will participate in the hospital's exercise program starting 5 to 7 days after HFS. All participants will follow the computer-based BSE program. Functional outcomes will be measured at 1 and 3 weeks as well as at 3 and 6 months after surgery. The trial has been registered prospectively with the Clinical Trials.gov Registry (NCT03618576) prior to participant recruitment. Important protocol modifications will be communicated to the trial registry.

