### Intervention

2.4

The post-HFS rehabilitation program will be delivered by a rehabilitation physician, physical therapist, occupational therapist, nutritionist, clinical nurse specialist, and social worker. The program consists of total 10 days of physical therapy (PT) sessions (twice per day for 60 minutes) during the 2 weeks after surgery. PT intensity (weight-bearing, strengthening, gait training, aerobic, and functional exercises) will be gradually increased based on the patient's functional level. Intensive patient education will also be provided by multidisciplinary rehabilitation members. BSE will be conducted with a computerized posturographic system for diagnosing balance and movement skills (Balance Master System NeuroCom; Natus Medical Inc., Pleasanton, CA) designed to objectively quantify balance and postural function of different origins, as described previously.^[13]^ Briefly, subjects will be prepared by being introduced to the supported standing position with the objective of looking for a symmetrical load on their legs. In the introductory session, dynamic exercises for small- and medium-sized muscle groups and lower extremity joints will be performed. Movements will be conducted at an average speed with maximum possible amplitudes. After the 5-minute introductory session, subjects will perform the main exercise for 20 minutes while maintaining the tandem position or maintaining their position with and without the use of a proprioceptive bubble. Subjects will be asked to walk on a rectilinear trajectory with or without crutches while changing speed and direction or while performing motor-cognitive tasks such as turning their head to the right and left side following a physiotherapist's input. At the final 5-minute session, the training load will be gradually reduced and conducted at a slow speed and maximum amplitude.

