### Data analysis

2.6

Data will be collected using a standardized data entry form and entered into the data management system. The intention-to-treat principle will be used for the data analysis. Participant characteristics will be described using means and standard deviations for continuous data and frequencies and percentages for categorical data. To compare paired data (before and after) between 2 different points, we will use the paired *t*-test and the Wilcoxon signed-rank test for continuous and nonparametric data, respectively. To compare categorical data, we will use McNemar's test. Statistical significance will be defined as a *P* value < .05. All statistical analyses will be performed using SPSS version 19.0 for Windows (IBM Corp., Chicago, IL).

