## Discussion

3

The balance problems of older populations are directly correlated with fragility fractures such as hip fractures that can cause serious morbidity and mortality. Therefore, it is necessary to anticipate and seek to solve such problems. Several types of balance training have been introduced in clinical settings. The main feature of the training is to allow maintenance of body position, both statically and dynamically, over the base of support within defined stability limits.^[27]^ Balance training has historically consisted of walking up and down stairs^[28–30]^ and/or walking on uneven surfaces (a rugged floor or fluffy sponge).^[31]^ Monticone et al^[32]^ suggested that balance task-specific training was superior to general exercises for improving physical function, balance, and ADLs in elderly patients who have undergone internal fixation following hip fracture. A computerized balance-training machine with a force plate that detects weight loads and a monitor giving visual feedback was recently used to train elderly subjects.^[33]^ Dodd et al^[34]^ showed that the training was feasible and useful after HFS in the elderly. However, no clinical trials of computerized balance training in elderly individuals after HFS have been reported to date. Our study will be the first to our knowledge to examine the efficacy and safety of computer-based BSE in this population.

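### The stated aim is the effectiveness of BSE, but a single-arm before/after test alongside full physical therapy measures change over time and cannot attribute it to BSE

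*Protocol article*

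**What the plan says.** **Aim.** The Objectives section says "We aim to evaluate the effectiveness of a computer-based balance specific exercise (BSE) on the performance and balance ability of the elderly women". A second sentence there asks whether the intervention lessens fear of falling and improves coping. The abstract also sets effectiveness of BSE as the purpose, and the Discussion says the study will be the first "to examine the efficacy and safety of computer-based BSE in this population".

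**Arms.** Under Trial design: "All participants will follow the computer-based BSE program". No control group, historical comparator or performance threshold is given.

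**Concurrent treatment.** Under Intervention: "The program consists of total 10 days of physical therapy (PT) sessions (twice per day for 60 minutes) during the 2 weeks after surgery". The same section adds that "PT intensity (weight-bearing, strengthening, gait training, aerobic, and functional exercises) will be gradually increased based on the patient's functional level", and that a multidisciplinary team gives intensive education.

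**Timing and outcome.** The primary outcome is the BBS, range 0 to 56. Measurements fall at week 1 (before the intervention), week 3 (after it), and 3 and 6 months after surgery.

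**Analysis.** Under Data analysis, the tests are those for use "To compare paired data (before and after) between 2 different points": paired t, Wilcoxon signed-rank and McNemar, with significance at P < .05.

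**Status.** Sample size and recruitment calls the trial preliminary, gives that as the reason for having no sample-size calculation, and sets the number at 40.

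**The concern.** The aim is causal and specific to one component of care. The Background even names the gain from balance rehabilitation taken by itself as the open question. The design observes only the whole package: recovery from surgery, progressive PT, education, repeated testing and BSE, all acting over the same weeks in the same patients. The null hypothesis of a paired test is zero mean change between two visits. Rejecting it says that patients at week 3 differ from patients at week 1. It does not say why.

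At stake is the primary conclusion. If a significant BBS change were taken as the answer to the stated aim, it would credit BSE with improvement that might have occurred without it. A larger sample would not help: it would only make significance more certain for any non-zero background change. No analysis plan can supply a comparator that the design does not have, so this is not a detail left to a fuller document.

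**Working it through.** The plan has no power figure to reproduce: 40 is stated without effect size, SD or power. The check therefore asks how often the planned test would be significant if BSE did nothing.

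**Inputs**
- n = 40 (Sample size and recruitment), all assumed to be analysed.
- α = .05 (Data analysis). Sidedness is not stated; two-sided is assumed.
- BSE effect = 0, set for this check.
- Background change d = mean BBS change from recovery, PT, education and repeat testing, divided by the SD of the change score. The article gives neither quantity, so d is varied from 0 to 0.8.

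**Formula.** The paired t statistic has n − 1 = 39 degrees of freedom and non-centrality λ = d√n = 6.325 d. The critical value is t(.975, 39) = 2.023. Then

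P(P < .05) = P(|T| > 2.023), with T non-central t on 39 df and parameter λ.

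| Assumed d | λ | P(P < .05) with zero BSE effect |
|---|---|---|
| 0 | 0 | 5% |
| 0.1 | 0.632 | 9% |
| 0.2 | 1.265 | 23% |
| 0.3 | 1.897 | 46% |
| 0.5 | 3.162 | 87% |
| 0.8 | 5.060 | 99.9% |

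**On the BBS scale, with assumed values.** A background gain of 2 points with an SD of change of 8 gives d = 2/8 = 0.25 and a probability of 34%. A gain of 5 points with an SD of 10 gives d = 0.5 and 87%.

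**Smallest significant result.** An observed mean change is significant once it exceeds 2.023/√40 = 0.32 SD of the change score. The same figure is the half-width of the 95% CI for the mean change.

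**Loss to follow-up.** If 20% were lost (an assumption), n = 32 and the probabilities fall to 38% at d = 0.3 and 78% at d = 0.5. The pattern is unchanged.

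**Would splitting the 40 patients answer the aim?** Take two arms of 20, a normal approximation, and an assumed between-arm difference δ in units of the outcome SD. Power = Φ(δ√(20/2) − 1.96). For δ = 0.5 this is Φ(1.581 − 1.96) = 35%; for δ = 0.8 it is Φ(2.530 − 1.96) = 72%. For 80% power at δ = 0.5, n per arm = 2(1.960 + 0.842)²/0.5² ≈ 63. So 40 patients could support a controlled comparison only if the difference were large.

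**The case against.** The strongest reply is that the study is openly preliminary and openly gives BSE to everyone, and that single-arm pilot studies are legitimate. All of that is true. But the word preliminary is used to waive a sample-size calculation; it does not limit the aim, which remains effectiveness in the abstract and Objectives and efficacy in the Discussion. The point does not require a second arm, only that the claim fit what one arm can show.

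Several stronger readings are tempting, and the document does not support them:

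- *That P < .05 is the declared criterion for effectiveness.* It is a general significance level. It is the only decision rule beside an effectiveness aim, but nowhere does the article say that a significant BBS change will count as proof that BSE works.
- *That the article itself concedes the null is false without BSE.* The Background says conventional programmes improve independence in daily activities and gait. It does not say so of the BBS, and it adds that they had no significant long-term effect on re-fracture and fall rates. Early recovery of balance is plausible, but the article does not state it.
- *That the false-claim rate is about 50–100%.* That holds only if the background change is roughly 0.3 SD or more. Below that, the figure runs down to 5%.
- *That the trial carries no information.* Little or no change in BBS would be informative, and safety can be described in one arm.
- *That occupational therapy sessions add to the confounding.* An occupational therapist is on the team, but no such sessions are described.

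**Conclusion.** The mismatch between aim and design is real and stands on the article's own text. The planned test addresses change over time in patients receiving PT plus BSE. A significant result cannot separate BSE from the other influences, whatever the sample size. The chance of significance with an inert BSE ranges from 5% to almost 100%, and where it falls depends on a background change that the article does not give; the range also rests on two-sided testing and complete data on 40 patients. The structural conclusion needs none of these assumptions. This should be corrected, because it governs what the primary result may be said to show and, after data collection, could be repaired only by withdrawing the claim.

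**What to change.** 1. **Abstract, Objectives and Discussion.** Replace effectiveness or efficacy of BSE with a description of change in balance and function, and of safety and feasibility, during a postoperative rehabilitation programme that includes BSE. Reword the sentence on fear of falling and coping in the same way, since it makes the same causal claim.
2. **Data analysis.** Make the primary result the mean BBS change from week 1 to week 3 with its 95% CI. State that P < .05 for a before/after change will not be interpreted as an effect of BSE.
3. **Use of the results.** Say that the study may supply variability, feasibility and safety data for a later controlled trial, but that the uncontrolled change is not an estimate of the difference between PT with BSE and PT alone.

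The cost is a few sentences, one confidence interval and a more modest claim. No extra patients and no change to treatment are needed. If the effectiveness aim is to be kept, a concurrent comparison with PT alone is required, and that is a different and probably larger trial.

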## Method

2

### Trial design

2.1

This prospective and open-label clinical trial will be performed in a tertiary hospital setting. During the 2-week postoperative intervention period, patients will participate in the hospital's exercise program starting 5 to 7 days after HFS. All participants will follow the computer-based BSE program. Functional outcomes will be measured at 1 and 3 weeks as well as at 3 and 6 months after surgery. The trial has been registered prospectively with the Clinical Trials.gov Registry (NCT03618576) prior to participant recruitment. Important protocol modifications will be communicated to the trial registry.

### Participants and eligibility criteria

2.2

Elderly female patients (≥65 years old) who have undergone surgery for femoral neck, intertrochanteric, or subtrochanteric fractures regardless of surgery type (internal fixation, bipolar hemiarthroplasty, or total hip arthroplasty) will be included. Patients who have experienced the following will be excluded: hip surgery for infection, arthritis, implant loosening, or avascular necrosis; femoral shaft fracture, acetabular fracture, isolated fracture of the greater or lesser tuberosity, or periprosthetic fracture; pathologic fracture; combined multiple fracture; revision surgery; severe cognitive dysfunction (obey command ≤ 1 step); cannot stand by supporting a fixed walker at 5 days postoperative; and refusal to participate in a clinical trial.^[12]^

### Sample size and recruitment

2.3

Because this study is a preliminary and open-label trial, sample size calculation is not needed. A total of 40 subjects will be consecutively recruited. All participants will be enrolled at one tertiary hospital. On the fifth day after HFS, patients who meet the inclusion but not the exclusion criteria will be preliminarily screened by researchers in cooperation with orthopaedic surgeons. Patients who agree to participate in the study will be enrolled.

### Intervention

2.4

The post-HFS rehabilitation program will be delivered by a rehabilitation physician, physical therapist, occupational therapist, nutritionist, clinical nurse specialist, and social worker. The program consists of total 10 days of physical therapy (PT) sessions (twice per day for 60 minutes) during the 2 weeks after surgery. PT intensity (weight-bearing, strengthening, gait training, aerobic, and functional exercises) will be gradually increased based on the patient's functional level. Intensive patient education will also be provided by multidisciplinary rehabilitation members. BSE will be conducted with a computerized posturographic system for diagnosing balance and movement skills (Balance Master System NeuroCom; Natus Medical Inc., Pleasanton, CA) designed to objectively quantify balance and postural function of different origins, as described previously.^[13]^ Briefly, subjects will be prepared by being introduced to the supported standing position with the objective of looking for a symmetrical load on their legs. In the introductory session, dynamic exercises for small- and medium-sized muscle groups and lower extremity joints will be performed. Movements will be conducted at an average speed with maximum possible amplitudes. After the 5-minute introductory session, subjects will perform the main exercise for 20 minutes while maintaining the tandem position or maintaining their position with and without the use of a proprioceptive bubble. Subjects will be asked to walk on a rectilinear trajectory with or without crutches while changing speed and direction or while performing motor-cognitive tasks such as turning their head to the right and left side following a physiotherapist's input. At the final 5-minute session, the training load will be gradually reduced and conducted at a slow speed and maximum amplitude.

### Outcome measures

2.5

The following demographic data will be collected at baseline: age, sex, fracture location and laterality, surgery type, and underlying disease. Functional outcomes will be measured at 1 (before intervention) and 3 (after 2 weeks’ intervention) weeks and at 3 and 6 months after surgery. The primary outcome of this study will be balance and fall risk assessed using the BBS^[14]^ (range, 0–56; a lower score indicates a worse outcome). The secondary outcomes will be as follows: physical functioning and walking ability assessed according to the FAC^[15]^ (range, 0–5; a lower score indicates a worse outcome), Koval walking ability scores^[16]^ (range, 1–7; with a higher score indicating a worse outcome), which rate physical functioning according to walking dependency, MRMI^[17]^ (range: 0–40; a lower score indicates a worse outcome), and the MFES^[18]^ (range: 0–140; a lower score indicates a worse outcome); cognition evaluated using the Korean version of MMSE^[19]^ (range: 0–30; a lower score indicates a worse outcome); mood evaluated using the Korean version of GDS^[20]^ (range, 0–30: a lower score indicates a worse outcome); QOL evaluated using the EQ-5D^[21]^ (range: 0–1; a lower score indicates a worse outcome); ADLs determined using the Korean version of MBI^[22]^ (range, 0–100; a lower score indicates a worse outcome) and the Korean version of the Instrumental ADL^[23]^ (range, 0–3; a higher score indicates a worse outcome); and frailty, assessed based on the Korean version of the Fatigue, Resistance, Ambulation, Illnesses, and Loss of weight scale (FRAIL) using the Korean version of the FRAIL scale^[24]^ (range, 0–5; a lower score indicates a worse outcome).

### Data analysis

2.6

Data will be collected using a standardized data entry form and entered into the data management system. The intention-to-treat principle will be used for the data analysis. Participant characteristics will be described using means and standard deviations for continuous data and frequencies and percentages for categorical data. To compare paired data (before and after) between 2 different points, we will use the paired *t*-test and the Wilcoxon signed-rank test for continuous and nonparametric data, respectively. To compare categorical data, we will use McNemar's test. Statistical significance will be defined as a *P* value < .05. All statistical analyses will be performed using SPSS version 19.0 for Windows (IBM Corp., Chicago, IL).

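### Intention-to-treat is promised, but the tests named for change use only patients measured at both time points, so as written each BBS change is an available-pair result

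*Protocol article*

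**What the plan says.** The promise appears twice. The abstract says "The data will be analyzed using the intention-to-treat principle", and section 2.6 (Data analysis) says "The intention-to-treat principle will be used for the data analysis".

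Section 2.6 then gives the methods for change: "To compare paired data (before and after) between 2 different points, we will use the paired *t*-test and the Wilcoxon signed-rank test". The t-test is meant for variables treated as continuous, and the signed-rank test is its nonparametric counterpart. It adds: "To compare categorical data, we will use McNemar's test". The threshold is "Statistical significance will be defined as a *P* value < .05". No other inferential method is named.

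Section 2.5 (Outcome measures) sets the schedule: "Functional outcomes will be measured at 1 (before intervention) and 3 (after 2 weeks’ intervention) weeks and at 3 and 6 months after surgery". It also says "The primary outcome of this study will be balance and fall risk assessed using the BBS", and that sentence names no primary time point. Section 2.1 gives every participant the balance exercise, so there is one arm and every efficacy result is a within-patient change. Section 2.3 fixes 40 patients without a sample size calculation, and gives no expected dropout.

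**The concern.** A paired test works on within-patient differences. A patient without a value at one of the two points has no difference and contributes nothing. In a single-arm trial, intention-to-treat can at most mean that every enrolled patient is analysed whatever her adherence. The named tests alone do not achieve that at any visit where a value is missing.

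Missing values are foreseeable. The patients are women aged 65 or over, followed to 6 months after hip fracture surgery, and the article's Discussion itself links these fractures to serious morbidity and mortality.

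Two things are at stake. If patients who recover less are lost more often, the mean change among those seen is too favourable, and there is no control arm in which the same distortion might partly cancel. In addition, the contrasts at 3 weeks, 3 months and 6 months may rest on different patients, so the recovery curve mixes true change with change in who is measured.

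**Working it through.** The plan states no figure that can be reproduced, so the check has three parts.

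**1. What the tests use.** With n = 40 (section 2.3) and an assumed loss fraction d at a visit, the pairs left number 40 × (1 − d):

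| Assumed loss | Pairs left | Standardised paired change detectable at 80% power |
|---|---|---|
| 0% | 40 | 0.454 |
| 5% | 38 | 0.467 |
| 10% | 36 | 0.480 |
| 20% | 32 | 0.511 |
| 30% | 28 | 0.549 |

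The last column uses the noncentral t distribution with alpha 0.05, taken as two-sided because the article does not say. As a direct check, a paired t-test on 40 simulated patients with 8 missing follow-ups gave 31 degrees of freedom, that is, 32 pairs. It returned no result when incomplete pairs were left in.

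**2. Bias by arithmetic.** The mean change in all enrolled is (1 − d) × (mean in those seen) + d × (mean in those lost). Therefore

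mean in those seen − mean in all = d × (mean in those seen − mean in those lost).

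Assume that lost patients would have gained 5 to 10 BBS points less than those seen:

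- d = 0.10: 0.10 × 5 = 0.5 to 0.10 × 10 = 1.0 point
- d = 0.20: 1.0 to 2.0 points
- d = 0.30: 1.5 to 3.0 points
- d = 0: zero

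**3. Paired analysis against a likelihood analysis.** All inputs are assumptions: n = 40; BBS means 15, 27, 36 and 40 at the four visits; SDs 10 to 11; correlations 0.5 to 0.8; 200 simulated trials per cell. The true 6-month change is 40 − 15 = 25.0. The likelihood estimate is multivariate-normal maximum likelihood on all observed values, which is what a repeated-measures model with unstructured covariance targets.

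| Dropout | Loss | Paired, both visits seen | Likelihood, all observed values |
|---|---|---|---|
| More likely after a small week 1 to 3 gain | 15% | 25.98 | 24.99 |
| | 25% | 26.33 | 24.86 |
| | 35% | 27.11 | 25.11 |
| Depends on week-3 level | 15% | 24.89 | 24.95 |
| | 25% | 25.07 | 25.06 |
| | 35% | 24.85 | 24.84 |

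Under the first mechanism the paired estimate is too high by 25.98 − 25.0 = 1.0, then 1.3, then 2.1 points. An independent repeat with 300 trials per cell gave 26.1, 26.3 and 27.0 for the paired estimate and 25.2, 24.9 and 25.0 for the likelihood estimate. Under the second mechanism neither method is biased to any visible degree.

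Simulation noise is small beside the first effect. With SDs 10 and 11 and correlation 0.5, the SD of change is √(100 + 121 − 110) = 10.5. With 40 × 0.65 = 26 patients, the standard error of a mean is 10.5/√26 = 2.1, and over 200 trials the simulation error is about 2.1/√200 = 0.15.

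**The case against.** A journal article condenses the plan, and the rule for missing values commonly sits in a full protocol or SAP, which is not shown here. Section 2.6 does not say that patients with a missing visit are excluded, and it does not rule out imputation before a paired test. This stands. A reader might infer that the named tests cannot deliver intention-to-treat at all; the text supports only that they do not do so by themselves. The point is therefore the mismatch between two things the article does state, and the better method available, rather than the absence of a missing-data rule.

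A reader might also infer that the results will describe treatment completers. The document does not support that. A patient who stops the exercise but attends follow-up stays in, which fits the adherence side of intention-to-treat. The restriction is to patients observed at both visits. It applies at week 3 too, although the week 1 to week 3 pair is close together and probably loses few.

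The size is assumed, and depends on the mechanism. An overstatement of 1.0 to 2.1 points on an assumed gain of 25 is 4 to 8%, which would hardly alter a before-after significance test. This also stands: the effect is on the estimate and its description.

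Finally, a mixed model is not a complete cure. Both simulated mechanisms depend on observed scores, where a likelihood method is expected to do well; loss depending on unobserved scores was not examined. The model also treats scores after death as if they were merely missing. It does not suit short ordinal scales such as FAC (0–5), Koval (1–7) and FRAIL (0–5), or outcomes analysed by McNemar's test. These limits shape the fix but do not remove the case for it on BBS.

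**Conclusion.** The concern holds in a limited form. On the article's own text, the promised principle and the named tests fit together only where no value is missing. Elsewhere, the BBS change is an available-pair result whose subset can differ between visits, chiefly at 3 and 6 months.

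The claim that recovery will be overstated would go too far. It could be, by about 1 to 2 BBS points at 15 to 35% loss if loss depends on early gain. The bias is about nil if loss depends on week-3 level, and zero if no one is lost. These figures rest on assumed means, SDs, correlations and dropout, since the document gives none of them. The point does not invalidate the trial, but it affects how the primary outcome is estimated and described, and it is cheap to correct.

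**What to change.** For BBS, and other scales treated as continuous, make the main analysis one mixed model for repeated measures:

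- time as a categorical fixed effect with unstructured covariance (4 visits give 4 × 5/2 = 10 covariance parameters);
- all enrolled patients with at least one assessment;
- estimated changes from week 1 to each later visit, with 95% confidence intervals.

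State that the model assumes data are missing at random. Report deaths and other losses by visit separately, because the model does not resolve scores after death. Keep the paired test as a sensitivity analysis.

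Keep Wilcoxon and McNemar for short ordinal and categorical outcomes, give the number of pairs at each visit, and label those results as available-pair rather than intention-to-treat.

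The cost is a change of wording and slightly more analysis with a standard procedure, using data already planned. The downside is reliance on the missing-at-random assumption. If no values are missing, the model's estimated mean change equals the mean paired difference, so nothing is lost on the estimate.
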